**Fig. 2 Fig2:**
[figure not shown]
Schedule of events. *Data will be collected if patients are still in the Intensive Care Unit. MV, mechanical ventilation; SOFA, Sequential Organ Failure Assessment score

### Outcome measures

The primary outcome is all-cause mortality at 60 days after randomization. Site investigators will be reporting patient status at 60 days, irrespective of whether the patient continued hospitalized in the same hospital, in another type of health care facility, or discharged home. If patients are discharged alive from hospital before day 60, the information on clinical status at 60 days will be obtained from the electronic clinical record. The Public Health Care System in Spain provides information about the clinical status of any patient through the electronic clinical record system that exists in any public hospital, city, province, or region. In the few cases in which no information could be not obtained from the electronic clinical record (e.g., the patient is not in contact with the outpatient clinic or home care professionals), the local investigator will contact the patient or relatives by phone to ensure the status of the patient at day 60 after randomization. In addition, lead investigators in each site will confirm the recorded 60-day mortality at the time of data analysis.

The secondary outcome is the number of VFDs at 28 days, defined as the number of days alive and free of MV from the day of randomization (day 1) to day 28 after enrollment, on which a patient breathe without assistance. For a day to be considered a ventilator-free day, the patient must breathe without assistance for the full 24 h, i.e., for every breath during that day. The following considerations will be taken into account when calculating the number of VFDs: (i) successful liberation from MV should last more than 48 h without reintubation in patients who survive 28 days after randomization; (ii) extubation only count from the last successful extubation within a 28-day survivor; and (iii) VFDs are awarded zero days if the patient is ventilated for 28 days or more, or die before 28 days (irrespective of intubation status) [20]. Other clinical outcomes include mortality in the ICU, mortality at day 28, duration of MV, length of stay in the hospital for survivors, and the time (in days) from treatment initiation to death. Virologic measures will include the proportions with viral RNA detection over time. Safety outcomes in both groups will include adverse events that occurred during treatment (hyperglycemia, new infections), serious adverse events, and premature discontinuation of treatment.

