**Methods/design:**

This is a multicenter, randomized, controlled, parallel, open-label, superiority trial testing dexamethasone in 200 mechanically ventilated adult patients with established moderate-to-severe ARDS caused by confirmed SARS-CoV-2 infection. Established ARDS is defined as maintaining a PaO_2_/FiO_2_ ≤ 200 mmHg on PEEP ≥ 10 cmH_2_O and FiO_2_ ≥ 0.5 after 12 ± 3 h of routine intensive care. Eligible patients will be randomly assigned to receive either dexamethasone plus standard intensive care or standard intensive care alone. Patients in the dexamethasone group will receive an intravenous dose of 20 mg once daily from day 1 to day 5, followed by 10 mg once daily from day 6 to day 10. The primary outcome is 60-day mortality. The secondary outcome is the number of ventilator-free days, defined as days alive and free from mechanical ventilation at day 28 after randomization. All analyses will be done according to the intention-to-treat principle.

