### Statistical analysis

Data will be collected in each participating ICU using a standardized form. Then, the data will be transmitted to the coordinating center whenever a patient dies or is discharged from the hospital. Before entering the data into a computerized database at the randomization center, a trained data collector will check the completeness and the quality of information. Logical checks will be performed for missing data and to find inconsistencies, especially regarding clinical diagnosis, date, and severity scores. If necessary, the data collector will contact the investigator by phone to validate the data or reformat the data for entry into the database. Automatic range and completeness checks are performed as data are entered into the database. All analyses will be done according to the intention-to-treat principle without adjustment for multiple comparisons for the secondary outcomes since these are considered exploratory in nature. Baseline characteristics will be summarized descriptively, as appropriate (i.e., means (SD) or median and quartiles for continuous variables and counts/percentages for categorical/binary variables). Primary and secondary outcomes will be reported as observed between-group differences with 95% confidence intervals (CI) and two-sided *p* values. The 60-day mortality will be compared using a chi-squared test, and the treatment effect will be expressed as a risk difference with 95% CI. The risk ratio and 95% confidence interval will also be computed. It is expected that the primary outcome will be ascertainable for everyone. Nevertheless, should missing outcomes be a problem, an inverse probability weighted analysis will be conducted. VFDs will be assessed with the Mann-Whitney *U* rank test. Since the nonparametric test works with ranks, it is usually not possible to get a CI with exactly 95% confidence. Thus, the 95% CI for the difference between medians for VFDs in both groups will be estimated using a bootstrap procedure (10,000 replications).

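### Read literally, the VFD rules can score a survivor still ventilated at day 28 above a matched patient who was successfully re-extubated (minor)

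*Protocol article*

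**What the plan says.** The Outcome measures section of the protocol article defines VFDs as "the number of days alive and free of MV from the day of randomization (day 1) to day 28 after enrollment". For a day to count, "the patient must breathe without assistance for the full 24 h". Three rules follow:

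- Rule (i): "successful liberation from MV should last more than 48 h without reintubation in patients who survive 28 days after randomization".
- Rule (ii): "extubation only count from the last successful extubation within a 28-day survivor".
- Rule (iii): "VFDs are awarded zero days if the patient is ventilated for 28 days or more, or die before 28 days", whatever the intubation status at death.

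The abstract words the outcome a little differently: "defined as days alive and free from mechanical ventilation at day 28 after randomization". Under Statistical analysis, "VFDs will be assessed with the Mann-Whitney *U* rank test", with a bootstrap interval for the difference in medians. Secondary outcomes are not adjusted for multiplicity, "since these are considered exploratory in nature".

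**The concern.** Rule (i) tests success by 48 h off the ventilator, not by freedom through day 28. Rule (iii) awards zero by duration of ventilation or by death, not by status on day 28. A 28-day survivor who was off the ventilator for more than 48 h, was reintubated and is ventilated on day 28 therefore meets neither condition for zero. The earlier extubation remains the last successful one, and the free days after it stand. If the same patient is then successfully re-extubated, rule (ii) moves the start of the count forward and those days are dropped. The score can fall because the patient recovered.

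VFDs are the one named secondary outcome and are compared by ranks, so a reversed pair enters the test directly. If late reintubation were more frequent in one arm, literal scoring could shrink that difference.

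**Working it through.** **Plan's own figure.** The article gives no numerical assumption for VFDs, so there is none to reproduce. The check applies the rules to patient records.

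**Notation.** Let *e* be the day of first extubation, *r* the day of reintubation (at least *e* + 3, so the first liberation is successful) and *x* the day of second extubation. Only full free days count, so a free spell runs from the day after extubation to the day before reintubation, or to day 28.

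**Literal scores for a 28-day survivor.**

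- Still ventilated on day 28: VFD = *r* − 1 − *e* (length of the first free spell).
- Re-extubated on day *x* and off thereafter: VFD = 28 − *x* (length of the second free spell).

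The order is reversed whenever *r* − 1 − *e* > 28 − *x*, that is, whenever the discarded first spell is longer than the second.

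**Examples.**

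| *e* | *r* | *x* | Still ventilated | Re-extubated | Order |
|---|---|---|---|---|---|
| 5 | 20 | 22 | 20 − 1 − 5 = 14 | 28 − 22 = 6 | reversed |
| 10 | 24 | 25 | 24 − 1 − 10 = 13 | 28 − 25 = 3 | reversed |
| 10 | 14 | 17 | 14 − 1 − 10 = 3 | 28 − 17 = 11 | correct |

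Reversal is thus a feature of late reintubation; after early reintubation the order is often right.

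**How far it reaches.** Enumerating *e* from 3, *r* from *e* + 3 and *x* up to day 27 gives 1,771 matched pairs: 946 reversed, 110 tied and 715 correctly ordered. With *r* on day 21 or later, 336 of 371 are reversed. If *x* is limited to day 26, so that more than 48 h off the ventilator can be shown by day 28, 715 of 1,540 are reversed. These are unweighted counts of day combinations, not patient frequencies.

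**Share of patients (assumed inputs, none in the documents).** Take 60% alive at day 28, 80% of those extubated, and 5–15% of extubated survivors reintubated after 48 h. Relapsers are 0.60 × 0.80 × 0.05 = 2.4% to 0.60 × 0.80 × 0.15 = 7.2% of randomized patients. Only those still ventilated on day 28 are scored differently by a day-28 zero rule. In simulation (first extubation uniform on days 5–21, reintubation 3–12 days later, mean 10 days to re-extubation) that is about 1.4–4.2%, or 3–8 of 200.

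**Effect on the planned test (same assumptions, 100 per arm, Mann-Whitney at 0.05).**

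| Late reintubation by arm | Rejection, literal rules | Rejection, zero if on MV at day 28 |
|---|---|---|
| 5% v 15% | about 5% | about 6% |
| 5% v 30% | about 10% | about 20% |

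In the 5% v 15% case the significance verdict was the same in about 98% of simulated trials.

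**Effect of changing a rule.** For *e* = 10, *r* = 24, *x* = 25 (still ventilated v re-extubated):

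- Zero if on MV at day 28: 0 v 3.
- No reset, all full free days counted: 13 v 13 + 3 = 16.

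Either change removes every reversal in the 1,771 pairs.

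**The case against.** The strongest reply is that the result depends on a reading. The rules are compressed and rest on a cited source. The abstract's wording may mean free of ventilation on day 28, and the authors may have meant rule (iii) to cover anyone ventilated then, or a successful extubation to be one never followed by reintubation. Either meaning removes the reversal. This stands as an account of possible intent, but not of the text: rule (i) sets a 48 h test and rule (iii) a duration. The day-5/day-20 record can score 14 (full free days), 28 − 5 = 23 (days since the last successful extubation) or 0 (presumed intent). Nor is this detail left to an analysis plan, since the article states the rules and they misorder patients when applied as written.

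A second reply is that 14 is a fair score under the base definition: the still-ventilated patient really had 14 free days, and the re-extubated one, with 14 + 6 = 20, is under-credited by the reset. That also stands. The fault lies in the combination of rules, and calling the still-ventilated patient over-scored presupposes a zero rule. For the same reason, that patient's 14 against 13 for someone extubated once on day 15 is no anomaly.

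A reader might infer that about half of relapsing patients will be misranked, or that the VFD comparison will conceal harm from new infections. The documents support neither. The 946 of 1,771 is not a frequency. The article lists new infections as expected events without tying them to late reintubation, and reports infections and duration of ventilation separately.

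**Conclusion.** The point holds as a defect in the scoring rules, of minor severity. Read literally, they can place a survivor who is ventilated on day 28 above a matched patient who recovered from the same relapse, mainly when reintubation is late. That follows from the text and needs no assumed rate.

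Its practical size does rest on assumptions, because the article gives no reintubation rate. Under those used here a few percent of patients are affected, and the planned rank test changes little unless late reintubation differs strongly between arms. The outcome is declared exploratory, and the 60-day mortality analysis and the sample size are untouched. The investigators may already intend zero for a patient ventilated on day 28; the current wording does not say so.

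**What to change.** Before the data are analysed:

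- In rule (iii), award zero if the patient dies before day 28 or is receiving mechanical ventilation on day 28 after randomization, in place of the criterion of ventilation lasting 28 days or more.
- In rule (ii), start the count at the last extubation after which the patient stays off mechanical ventilation through day 28, keeping the 48 h requirement.

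This takes one or two sentences and no new data, since the rules already need the extubation and reintubation dates. It does not affect patient care.

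The price is that a few late-relapse survivors score zero and mean VFDs fall slightly. It also creates a cliff: a patient extubated on day 5 and reintubated on day 28 goes from 28 − 1 − 5 = 22 to 0. If that is unwelcome, dropping the reset in rule (ii) and counting all full free days also removes the reversal. Either choice is workable if fixed in advance.

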Other continuous outcome variables will be compared with the Student’s *t* test. The treatment effect will be expressed as mean differences with 95% confidence intervals. For variables where there are major concerns about the underlying assumptions for the *t* test, the Mann-Whitney *U* rank test will also be used for a sensitivity analysis. Other categorical outcome variables will be compared using a chi-square test or Fisher’s exact test if expected counts are < 5. The treatment effect will be expressed as a risk difference with 95% confidence interval as well as the risk ratio. The time to hospital discharge will be summarized with cumulative incidence curves, treating death as a competing risk and compared using a cause-specific Cox model, and the treatment effect will be expressed as a hazard ratio with 95% confidence interval. Two-sided testing will be used for all inferential comparisons. A *p* value of less than 0.05 will be considered to indicate statistical significance for the primary outcome. Given the controversies around significance testing, *p* values will always be accompanied by point estimates of treatment effect and 95% confidence intervals. Analyses will be done by an independent statistician who will be unaware of group assignment.

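### Duration of mechanical ventilation has no stated population or rule for deaths and falls to a t test, so at the planned mortality rates its mean difference can mislead in either direction

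*Protocol article*

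**What the plan says.** Outcome measures, after the primary and secondary outcomes: "Other clinical outcomes include mortality in the ICU, mortality at day 28, duration of MV, length of stay in the hospital for survivors". Hospital stay is restricted to survivors. Duration of mechanical ventilation (MV) has neither a population nor a rule for patients who die on the ventilator.

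Statistical analysis gives the default: "Other continuous outcome variables will be compared with the Student’s *t* test", with the effect expressed as a mean difference. Where the t test's assumptions are in serious doubt, "the Mann-Whitney *U* rank test will also be used for a sensitivity analysis".

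Two neighbouring outcomes do take account of death:
- Ventilator-free days (VFDs), the secondary outcome: "VFDs are awarded zero days if the patient is ventilated for 28 days or more, or die before 28 days (irrespective of intubation status)".
- Discharge: "The time to hospital discharge will be summarized with cumulative incidence curves, treating death as a competing risk and compared using a cause-specific Cox model".

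The secondary outcomes are analysed "without adjustment for multiple comparisons for the secondary outcomes since these are considered exploratory in nature".

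**The concern.** Every patient is intubated at entry, and about half of the control group is expected to die, so death often ends ventilation. A t test or rank test on days of ventilation must do one of two things:

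- **Include everyone.** Death on the ventilator then ends the count and scores as short ventilation, the same direction as a good result.
- **Include survivors only.** The groups are then selected by an event after randomization that the drug is meant to change.

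Either way the mean difference mixes any effect on weaning with the effect on mortality. Mann-Whitney does not help, because it addresses the shape of the distribution and not death.

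The outcome will be read. Shorter ventilation is part of the hypothesis in the abstract. The earlier trial's 5-day reduction is part of the justification, and earlier liberation is among the benefits expected in the Discussion.

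**Working it through.** **The plan's own figure.** Sample size calculations: 55% versus 35%, two-sided 0.05, 80% power, mean rate 0.45.

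n per arm = [1.960·√(2·0.45·0.55) + 0.842·√(0.55·0.45 + 0.35·0.65)]² / 0.20² = 95.9, so 96.

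This matches the stated 96 per arm. The document gives no figure for duration of MV, so every duration below is assumed.

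**Strata.** If the drug causes no deaths, 45% of patients survive on either arm, 20% survive only on dexamethasone (the saved patients), and 35% die on either arm. The saved share of dexamethasone survivors is 0.20/0.65 = 31%.

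**Formulas.** Let *a* be mean MV days in patients who survive on either arm, *s* in saved patients, and *d* mean days to death on the ventilator. With no drug effect on *a* or *d*, dexamethasone minus control is:
- all patients: 0.20·(*s* − *d*)
- survivors only: 0.20·(*s* − *a*)/0.65

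**Sign, all patients, every survivor at 20 days:**

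| Mean days to death | Control | Dexamethasone | Difference |
|---|---|---|---|
| 12 | 0.55·12 + 0.45·20 = 15.6 | 0.35·12 + 0.65·20 = 17.2 | +1.6 |
| 24 | 0.55·24 + 0.45·20 = 22.2 | 0.35·24 + 0.65·20 = 21.4 | −0.8 |

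**Varying the saved patients' duration** (*a* = 16, *d* = 12). The last three columns come from a simulation of 3,000 trials with 100 patients per arm, gamma durations of shape 2.5, capped at 60 days:

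| *s* | All patients | Survivors only | t test significant for longer MV, all patients | Same, survivors only | Mean VFD difference |
|---|---|---|---|---|---|
| 16 | +0.8 | 0 | 9% | 2% | +2.6 |
| 22 | +2.0 | +1.8 | 29% | 12% | +1.9 |
| 28 | +3.2 | +3.7 | 53% | 32% | +1.3 |

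About 2.5% would be expected by chance in that direction. In all three rows VFDs favour dexamethasone while the all-patient MV difference points the other way.

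**With a true benefit.** Shorten *a* by 2 days, with *s* = 22 and *d* = 12:
- all patients: −0.45·2 + 0.20·(22 − 12) = +1.1 days
- survivors only: (0.45·14 + 0.20·22)/0.65 − 16 = +0.5 days

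Dexamethasone looks worse in both.

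**When the distortion vanishes.** The all-patient comparison is undistorted if *s* = *d*, and the survivors-only comparison if *s* = *a*.

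**Would a cause-specific hazard ratio be enough?** Take *a* = 20, *s* = 30 and *d* = 12, with gamma durations and a large simulated sample. The hazard ratio for liberation is about 1.00. The cumulative incidence of liberation is about 35% versus 46% at day 28 and 45% versus 63% at day 60. The ratio censors deaths, so alone it can hide a benefit that the curves show.

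**The case against.** **VFDs already carry the ventilation question.** They are the named secondary outcome and score death before day 28 as zero. The stated goal is mortality and VFDs. This stands: it limits the consequence but does not repair the separate MV-duration comparison.

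**These outcomes are low in the hierarchy.** They rank below a secondary outcome whose analysis is itself called exploratory, and the 0.05 threshold is tied to the primary outcome. This stands too.

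**A fuller protocol or analysis plan may give the population and death rule.** That is fair for the missing detail. The test, however, is stated in the article, and it does not fit the outcome whichever population is chosen.

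**The durations are invented.** They are assumptions, so only a range can be given. A reader might infer that the analysis is biased against the drug whenever it saves lives. The documents do not support that. It needs saved patients to be ventilated longer than those who die (all patients) or longer than other survivors (survivors only). Both are plausible, neither is documented, and the 24-day case reverses the sign.

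**Hospital stay is already handled.** A reader might infer that stay in survivors will also be t-tested. The article never says so. The default sentence could cover it, but the same paragraph gives discharge its own competing-risk analysis. What remains is a mismatch of labels: Outcome measures names stay in survivors, Statistical analysis names time to discharge, and neither says which governs.

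**Conclusion.** The point holds for duration of MV. The stated rule leads to a comparison that death distorts, although the plan uses death-aware methods for two closely related outcomes. At 55% versus 35% mortality the all-patient mean difference moves by +1.6 to −0.8 days in the 20-day example, and by +0.8 to +3.2 days in the 16-day example, without any drug effect on weaning in patients who would survive anyway. The survivors-only shift in the second example is 0 to +3.7 days. These figures rest on the planned mortality rates, on the drug causing no deaths, and on assumed durations.

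For hospital stay only a clarification is needed. The 60-day mortality and VFD analyses are unaffected. The practical risk is a published MV-duration result that contradicts the VFD result and is taken at face value. The change is worth making, but the trial's main conclusions do not depend on it.

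**What to change.** 1. Analyse duration of MV as time from randomization to successful extubation in all randomized patients, with death as a competing event.
2. Report cumulative incidence curves by arm and the difference in cumulative incidence at one fixed day (28 or 60, chosen in advance) with a 95% CI. Give the cause-specific hazard ratio alongside, not alone.
3. Report MV days in survivors descriptively.
4. State that the competing-risk analysis of time to discharge is the between-arm comparison for hospital stay, and that stay in survivors is descriptive.

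The cost is analysis wording and a little more analysis work. The extubation and death information is already needed for VFDs. The downside is that the result is less directly comparable with earlier trials that reported mean MV days. The descriptive survivor figures recover part of that.

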### Randomization and masking

Eligible, consented patients will be randomly assigned in a 1:1 ratio to receive either dexamethasone plus standard intensive care or standard intensive care alone (control group). Dexamethasone will be freely provided by the health authorities in participating hospitals. Because of the emergency nature of the trial, a placebo will not be used. According to the ethical principles for medical research of the Declaration of Helsinki [12], the use of no placebo (no intervention) is acceptable when no proven intervention exists. The Spanish Agency of Drugs and Medical Devices and the Ethics Committees did not mandate a blinded design or the administration of a placebo. Central randomization will be done within the REDCap system. Local investigators in participating ICUs are the only authorized personnel to interact with the web-response system through a username and password. Once eligibility is confirmed in the eCRF, the next available treatment group is assigned by the system according to a randomization schedule prepared by a statistician and uploaded as a look-up table to the REDCap system. The computer-generated randomization schedule will use random permuted blocks of varying sizes to further ensure allocation concealment and is unavailable to those who enroll patients or assign interventions.

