### Dexamethasone therapy and general procedures

Patients assigned to the dexamethasone group will receive the first dose immediately after being randomized. Patients in the dexamethasone group will receive an intravenous dose of 20 mg once daily from day 1 to day 5, and 10 mg once daily from day 6 to day 10. We selected the same doses as reported in the only published trial with dexamethasone in ARDS patients [8]. Treatment with dexamethasone will be given for a maximum of 10 days after randomization, independently of the intubation status (Fig. 1). Criteria for discontinuing intervention (exiting the trial) for a given trial participant are contemplated in the informed consent from (at patient’s legal representative request). In addition, as a request by the patient’s legal representative, allocated intervention (daily dose of intravenous dexamethasone) could be modified in case of a profound worsening of disease status (request to do-not-resuscitate orders, withdrawal of treatment and life support measures).

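### Time to death starts at treatment initiation, which controls do not have, and the only stated test rule that covers it can use only patients who died

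*Protocol article*

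**What the plan says.** The Outcome measures section ends its list of other clinical outcomes with "the time (in days) from treatment initiation to death". It gives no analysis population and no censoring rule for it, although in the same list it limits length of stay to survivors.

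The other clocks in the trial start at randomization. For the primary outcome: "The primary outcome is all-cause mortality at 60 days after randomization". Ventilator-free days and the 60-day follow-up use the same origin.

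On the control arm, Randomization and masking assigns standard intensive care alone and adds: "Because of the emergency nature of the trial, a placebo will not be used". For the active arm, Dexamethasone therapy and general procedures says: "Patients assigned to the dexamethasone group will receive the first dose immediately after being randomized".

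On method, Statistical analysis has a general rule: "Other continuous outcome variables will be compared with the Student’s" t test, with the effect as a mean difference, and with Mann-Whitney as a sensitivity analysis where the t test assumptions are in doubt. The one time-to-event method in the section (cumulative incidence curves and a cause-specific Cox model) is assigned to time to hospital discharge. Time to death is not mentioned there.

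**The concern.** There are two linked problems.

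First, the origin. A control patient never starts trial treatment, so the definition cannot be applied to half of the trial. A site that took treatment to mean standard care would start the control clock before randomization, because eligibility requires a reassessment 12 ± 3 h after ARDS diagnosis. A patient allocated to dexamethasone who never received a dose would have no start either, which does not fit the commitment to analyse by intention to treat.

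Second, the method. An outcome in days that is neither primary nor secondary, and is not time to discharge, falls under the rule for other continuous variables. Only patients who died have a value to enter. If the drug changes who dies, the dead in the two arms are no longer comparable groups, and their mean difference is not a treatment effect. It could be read as earlier death on dexamethasone in a trial where dexamethasone lowered mortality.

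**Working it through.** **Inputs from the protocol article.** 60-day mortality 55% control and 35% dexamethasone, two-sided alpha 0.05, power 80%, 96 per arm, 200 randomized (Sample size calculations); follow-up 60 days (Clinical and laboratory monitoring).

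**Assumed.** The article gives no distribution of death times. I used a constant hazard, and two-piece hazards with a break at day c = 7, 10 or 14 and 30%, 40% or 50% of control deaths before the break.

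**1. The plan's own figure.** n = [1.96·√(2·0.45·0.55) + 0.8416·√(0.55·0.45 + 0.35·0.65)]² / 0.20² = (1.379 + 0.580)² / 0.04 = 95.9, so 96 per arm. This reproduces.

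**2. Who enters the comparison.** With 100 per arm, 55 controls and 35 dexamethasone patients have a death time. The other 45 and 65, together 110 of 200, drop out, unequally and by the primary outcome itself. Mann-Whitney on observed death times loses the same patients.

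**3. Benefit only after the break (worked case: c = 10, 40% of control deaths before it).**
- Deaths by day 10 in both arms: d = 0.55 × 0.40 = 0.22, so S(10) = 0.78 and h1 = −ln(0.78)/10 = 0.02485 per day.
- Later hazard, control: [−ln(0.45) + ln(0.78)]/50 = 0.01100. Dexamethasone: [−ln(0.65) + ln(0.78)]/50 = 0.00365.
- Restricted mean survival to day 60, control: 0.22/0.02485 + (0.78 − 0.45)/0.01100 = 8.85 + 30.00 = 38.85 days. Dexamethasone: 8.85 + (0.78 − 0.65)/0.00365 = 8.85 + 35.65 = 44.51 days. Difference **+5.65 days**.
- Mean time to death among the dead = [restricted mean − 60·S(60)] / [1 − S(60)]. Control: (38.85 − 27)/0.55 = 21.5 days. Dexamethasone: (44.51 − 39)/0.35 = 15.7 days. Difference **−5.8 days**.

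The same patients thus gain survival time while the comparison among the dead points to harm.

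**4. All scenarios.**

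| Assumption | Difference among the dead | Restricted mean difference, all patients |
|---|---|---|
| Benefit only after day 7, 10 or 14 | −3.85 to −7.86 days | +5.07 to +6.14 days |
| Proportional hazards, two-piece | +1.80 to +1.89 days | +7.37 to +9.17 days |
| Proportional hazards, constant | +1.80 days (26.05 to 27.85) | +7.42 days |

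**5. How the t test would behave (5,000 simulated trials, 100 per arm).** With benefit only after day 10 and 40% or 50% of control deaths before it, the difference has the wrong sign in 94% and 99% of trials and is significant in the wrong direction in 34% and 59%. Under proportional hazards (constant, or two-piece with the day-10 break) the sign is wrong by chance in 32 to 33%, and the test is significant at all in about 7 to 8%.

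**6. A censored comparison under proportional hazards.** HR = ln(0.65)/ln(0.45) = 0.539. With 55 + 35 = 90 deaths, Schoenfeld power = Φ(√90/2 × 0.617 − 1.96) = Φ(0.967) = 83%.

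**The case against.** The strongest reply is that the article never names a t test for time to death. The conclusion is reached by elimination, and the statisticians plainly know censored methods, since they treat death as a competing risk for discharge. A statistical analysis plan, not shown here, may give a suitable method. This stands as a limit on the claim: a reader might infer that the plan prescribes a t test here, and the text does not say so. What remains is that the article's general rule, followed as written, covers this outcome, and only time to discharge is excepted.

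The origin also matters little numerically. Dexamethasone starts immediately after randomization, and dosing and the ventilator-free-day count both begin on day 1, so in that arm the two origins coincide on a scale of days. That stands too. The defect is mainly one of definition: controls lack a start.

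A reader might infer that the result will have the wrong sign. The documents do not support this. They give no death-time distribution, the reversal needs the benefit to fall on later deaths, and under proportional hazards the expected sign is right.

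A reader might also infer a threat to the trial's main conclusion. There is none. The outcome stands last among the other outcomes, below a secondary outcome that is itself called exploratory. The significance threshold is attached to the primary outcome, no sample-size or stopping decision uses time to death, and 60-day, 28-day and ICU mortality are all to be reported beside it.

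**Conclusion.** The point holds as a minor to moderate defect in an exploratory outcome. The origin is undefined in the control arm and out of line with every other endpoint. The only stated rule that covers the outcome would compare about 55 with 35 dead patients per 100 at the planning rates and so condition on the primary outcome.

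In size: about 4 to 8 days in the wrong direction if benefit falls only on deaths after day 7 to 14; the right expected sign but a nearly uninformative comparison under proportional hazards (7 to 8% significant, against about 83% power for a censored analysis). These figures rest on the planning mortality rates and on assumed hazard shapes; that the generic rule applies is an inference from the text. The 60-day mortality analysis is unaffected.

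**What to change.** In Outcome measures, define the outcome as time from randomization to death in all randomized patients, censored at day 60 or at the date last known alive. In Statistical analysis, add that it will be shown as Kaplan-Meier curves by arm with one pre-specified censored comparison, for example a Cox hazard ratio with a log-rank test, and exclude it from the rule for other continuous variables. A difference in restricted mean survival to day 60 would serve equally well; the need is to choose one in advance. If the analysis plan already does this, only the origin and a cross-reference need changing.

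The cost is about two sentences. The date of randomization, the date of death and the 60-day status are already needed for the planned outcomes, so no new data are required and the sample size does not change.
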